**Methods:**

This ongoing, randomized controlled intervention was designed with a six month follow-up study. The intervention consisted of three-hour weekly classes during a six week period with printed materials provided. Five of the classes were hands-on cooking and one was a tour to a popular food market. There were eight primary outcome measures: changes in relation to i) accessibility and availability of fruits and vegetables; ii) cooking attitudes; iii) cooking behaviors at home; iv) cooking behaviors away from home; v) produce consumption self-efficacy; vi) self-efficacy for using basic cooking techniques; vii) self-efficacy for using fruits, vegetables, and seasonings (while cooking); and viii) knowledge of cooking terms and techniques. Secondary outcomes included changes in body mass index and in personal characteristics related to cooking. Repeated measures were collected through the application of an online self-completed survey, at baseline, after intervention and six months after intervention. A sample of 80 university students (40: intervention group; 40: control group) was estimated to detect a mean change of 1.5 points in cooking knowledge, with study power of 80%, and 95% level of confidence, plus 20% for random losses and 10% for confounding factors. The control group participants have continued with their usual activities. Data analyses will evaluate the intervention effect on changes in outcomes within and between groups, as well as explore relations with personal characteristics.

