## Methods/design

### Study design

This study used a randomized controlled trial design with six months of follow-up (with repeated measures) to test a community-based cooking skills program to improve cooking and healthy eating behaviors in university students. The study started in 2015 with follow-up studies planned for 2016 and 2017.

The intervention program occurred over a two-month period, one day a week for eight weeks, with two weeks having no intervention topics (due to holiday schedule). The intervention group (IG) data was analyzed at three-time points: (1) on the week prior to the program’s beginning (T1); (2) on the completion of the eight-weeks program (T2); and (3) after six months, on the intervention follow-up period (T3). The control group (CG) comprised participants from the wait-list group who were waiting for 12 months to participate in the study as they continued with their usual practices. Data from this group was analyzed at the same three-time points before they began participation in the program and subsequent comparison with the IG data. After that, the CG will be invited to take part of the NCK program in order to be able to receive the program benefits. Once the study is ongoing, the control group will be invited to participate in the NCK program at the next stage of the study. Thus, the impacts of the intervention program will be evaluated immediately following the post intervention (T2) and the sustained effect, six months after the program (T3) [34, 35] for both groups (CG & IG).

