### Sample size calculation

Sample size calculation for the intervention aimed at detecting changes in the average values of the outcome related to cooking skills knowledge [32]. Considering a difference of 1.5 points in average [32], with study power of 80%, an error rate of 5% and a 95% level of confidence, a sampling plan of 28 students was estimated. Including a random loss of 20% and 10% for possible confounding factors, a minimum sample of 40 students was suggested to be investigated in each group (intervention & control), involving a total sample of 80 participants. Sample size calculation was carried out with the statistical program Open Epi version 3.03 (Open Source Epidemiologic Statistics for Public Health, Atlanta, GA, USA).

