### Outcomes measures

#### Primary outcomes

i) accessibility and availability of fruits and vegetables; ii) cooking attitudes; iii) cooking behaviors at home; iv) cooking behaviors away from home; v) produce consumption self-efficacy; vi) self-efficacy for using basic cooking techniques; vii) self-efficacy for using fruits, vegetables, and seasonings (while cooking); and viii) knowledge of cooking terms and techniques; assessed at baseline, immediately after intervention, and six months after intervention.

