### Statistical analysis

Descriptive analysis of the sociodemographic variables and of the student characteristics at baseline will be conducted with measures as mean and standard deviation for symmetrical numeric variables, or median and interquartile interval for asymmetrical numeric variables. For categorical variables, the description involves the prevalence of data (absolute and relative frequencies).

T-test (for parametric data) or Mann-Whitney test (for non-parametric data) will be run to verify the differences intragroup, among control groups and intervention for the pre-intervention condition (baseline) with continuous variables. For categorical and parametric variables, chi-square test or chi-square fisher’s exact test will be used.

Intervention’s effect will be evaluated by means of the analysis on the changes in cooking skills and healthy eating survey. Issues related to the scales evaluated by the instrument (in T1, T2, and T3) will be analyzed to verify data normality. Subsequently, ANOVA for repeated measures (for parametric data) or Friedman (for non-parametric data) followed by Wilcoxon signed rank test (post-hoc test) will be employed.

Data collected through the online survey will be transferred to Microsoft Office Excel® and exported to Stata® version 13.0 (Statacorp, College Station, TX, USA). Statistical analysis will be run on Stata® and a significance level of 5% will be adopted, considering *p* < 0.05.

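### Eight unranked primary outcomes share one plain 5% level with no rule for overall success, while the power calculation covers cooking knowledge only

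*Protocol article*

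**What the plan says.** The Abstract (Methods) states: "There were eight primary outcome measures". The Primary outcomes section repeats the same eight scales, each "assessed at baseline, immediately after intervention, and six months after intervention". Neither place puts one scale or one follow-up first, or says whether success means one, several or all of the eight. Study design adds that impact will be judged at T2 and the sustained effect at T3.

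For the effect analysis, the Statistical analysis section says that "ANOVA for repeated measures (for parametric data) or Friedman (for non-parametric data) followed by Wilcoxon signed rank test (post-hoc test) will be employed". It closes with the only error-rate rule in the article: "a significance level of 5% will be adopted".

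The Sample size calculation section "aimed at detecting changes in the average values of the outcome related to cooking skills knowledge". It uses a 1.5-point difference, 80% power and 5% error to reach 28 students, raised to 40 per group for losses and confounding. Eventual enrolment was 41 per group (Sample recruitment and selection).

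**The concern.** The primary outcomes, the significance level and the basis for power are all stated, and they do not fit together. With eight co-equal primaries each judged at 5%, a reader can call the trial positive on whichever scale crosses the line, and the chance of that under no effect is well above 5%. The remedy has a price the article does not show: once the level is divided among eight scales, the 80% power no longer holds even for the one outcome that was sized.

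The Discussion expects the results to be high-quality evidence and to inform public policy. A chance finding on one of eight scales could then carry more weight than it should.

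**Working it through.** **Inputs.** Eight primary outcomes (Abstract; Primary outcomes). Two follow-ups, T2 and T3 (Study design). Level 0.05, taken as two-sided (Statistical analysis). Difference 1.5 points, 80% power, 28 raised to 40 per group (Sample size calculation). Enrolment 41 per group. The article gives no SD and no correlations between scales or visits, so these are assumed below.

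**1. The plan's own figure.** No SD is stated, so 28 cannot be reproduced independently. The step 28/(1 − 0.30) = 40 per group supports reading 28 as per group. Solving n = 2(1.96 + 0.842)²·SD²/1.5² for n = 28 gives SD ≈ 2.0. Check: 2 × 7.85 × 4/2.25 = 27.9, so 28. The standardised difference is 1.5/2.0 = 0.75.

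**2. Chance of at least one false positive, eight tests at 0.05.**
- Independent: 1 − 0.95⁸ = 33.7%.
- Correlated (simulation from a multivariate normal with equal correlation between scales):

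| Correlation | 0.3 | 0.5 | 0.7 | 0.8 |
|---|---|---|---|---|
| Chance | 30% | 25% | 19% | 16% |

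**3. If T2 and T3 are tested separately (16 tests).**
- All independent: 1 − 0.95¹⁶ = 56.0%.
- With correlation 0.5 to 0.7 between visits on the same scale:

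| Correlation between scales | 0.3 | 0.5 | 0.7 | 0.8 |
|---|---|---|---|---|
| Chance | 45–48% | 38–41% | 30–32% | 25–27% |

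**4. The opposite success rule.** If all eight scales had to succeed, type I error would not be inflated. With 80% power on each scale, joint power would be 0.8⁸ = 17% if independent, 42% at correlation 0.5 and 53% at 0.7.

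**5. Power for knowledge after adjustment** (standardised difference 0.75, SD 2.0 assumed). The two sample sizes are 28 per group (the plan's base figure) and 33 (41 × 0.80 = 32.8, enrolment less the plan's 20% loss).
- Bonferroni, level 0.05/8 = 0.00625. Normal approximation: the expected z is 0.75·√(28/2) = 2.81 against a critical value of 2.73, giving power 53%. At 33 per group the expected z is 3.05 and power is 62%. Noncentral t gives 49% and 59%.
- Holm can never do worse than Bonferroni. If only knowledge responds, simulated power is about 53% (28) and 62% (33), the Bonferroni value. If all eight scales respond equally, it rises to about 62–65% (28) and 72–76% (33), with the higher figures at low correlation.
- If all 41 per group were analysed, noncentral-t Bonferroni power would be 72%, still under 80%.

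**The case against.** Several points on the other side stand.

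- **Number of tests.** A repeated-measures ANOVA or a Friedman test can yield one overall test per scale, with the visits entering only as post-hoc comparisons. A reader might infer from the two follow-ups that 16 tests at 5% are planned. The Statistical analysis section does not say that. Eight is the safe count, and the figures for 16 are conditional.
- **Size of the inflation.** It is tempting to say that the risk is at least one in four. That is the value for eight tests at one assumed correlation of 0.5. The scales come from one self-report questionnaire and three of them measure self-efficacy, so higher correlations and a lower risk are possible.
- **Success rule.** The inflation matters only if any single significant scale counts as success. The article does not say so, and it does not say otherwise.
- **Power claim.** A reader might infer that the article claims 80% power for all eight outcomes. It does not: the Abstract and the Sample size calculation section both tie the figure to cooking knowledge.
- **Silence on adjustment.** An analysis plan not shown could add a correction, so the absence of one is not in itself a fault.
- **Choice of primary.** Making knowledge the sole primary is partly a preference, since Theoretical perspectives calls self-efficacy a central construct.

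These points narrow the concern without removing it. The article itself fixes eight unranked primaries beside a plain 5% level, and any later correction would change the power of the one outcome that was sized.

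**Conclusion.** The point holds in a limited form. As written, and if any one significant scale is read as evidence of effect, the chance of at least one false-positive primary result under no effect is about 16–34% with one between-group test per scale, three to seven times the nominal 5%. The range rests on assumed correlations of 0.8 to 0. Testing T2 and T3 separately would raise it to about 25–48% at between-scale correlations of 0.8 to 0.3, and to 56% if all 16 tests were independent.

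The stated 80% power is valid only for knowledge, at an unadjusted 5%, and the other seven primaries have no power basis. The error-rate figures do not depend on the SD. The adjusted-power figures do: they rest on an SD of 2.0 inferred from the plan's 28 per group.

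**What to change.** Keep the eight scales as one primary family and control the overall error at 5% with Holm's procedure, applied to the between-group comparison for each scale. Say in the Sample size calculation section that the 80% power refers to cooking knowledge at an unadjusted 5%. Give the adjusted power alongside it: about 49–53% (Bonferroni floor) to 65% (Holm, all scales responding) at 28 analysed per group, and about 59–62% to 76% at 33, with the SD assumption stated.

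Alternatively, name the powered outcome as the single primary: cooking knowledge, intervention against control at T2, then T3 in fixed sequence, each at 5%. The other seven scales become secondary with Holm. This is credible only if no comparison by arm has been seen. The study began in 2015 and had follow-ups planned for 2016 and 2017, so that should be confirmed and recorded first.

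The cost is a little analysis work and amended protocol and registry wording. In return the sponsor accepts lower power per scale under the first route, or softer claims for seven scales under the second. No extra participants are needed.

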## Discussion

The evaluation of the NCK program may contribute to the growth of scientific literature in relation to the effectiveness of community-based culinary interventions. The randomized controlled methodological design with a follow-up after intervention will allow the researchers to analyze the sustained effect of the program on the eating practices of the chosen population. In addition, the methodological design described in this paper will permit the comparison of results with other culinary intervention programs conducted with similar populations. Since it is the first culinary intervention study conducted in Brazil that is controlled and randomized, as well as the first sustained impact study with university students at an international level, the study may contribute to the generation of scientific knowledge to develop public policies that aim at promoting healthy eating by means of the practice of cooking skills with this population.

This paper also provides practical information about the design and presentation of community-based interventions, including clear details about the program and the recruitment of the intervention and control groups. The use of recipes that were developed, adapted and tested for the objectives of the NCK program and to the target population of this study may contribute to the retention of participants in the program, as well as to the development of cooking skills and healthier eating habits.

The present study also presents some limitations. The population of the study belongs to only one public university, a fact that does not allow for the generalization of results. However, the chosen university has more than 30,000 enrolled students in undergraduate courses. Students come from several regions of Brazil and South American countries, which may contribute an increased diversity within the study sample. The inclusion of students from the same university cannot guarantee that the control group will not be influenced by the intervention group. When the control group waits until the study concludes to receive the intervention it can present limitations. During the waiting period, they may have experiences that may impact study outcomes [68]. Nevertheless, randomization procedures within the study groups remain the only method that could eliminate possible selection and confounding biases [69]. The chosen university has faculty, employee, and student population of 50,000 who circulate every day on campus. Thus, the likelihood of students meeting and influencing counterparts on culinary skills may be diminished. As such this factor presents a limitation on community-based intervention studies in general.

Additionally, the online survey was composed of questions that were answered by the participants themselves, which may allow for some information bias. For the BMI classification, data about weight and height provided by the participants themselves were used, which likewise may allow bias in regards to underestimation of weight or overestimation of height. Such bias may occur with overweight participants who tend to underestimate their weight [70]. However, self-reported measures of weight and height have been considered valid in epidemiologic studies and may be used to improve accuracy of the collected data [71].

Given that the study involves a six month follow-up, it is prone to have subject losses during the follow-up period. However, contact with participants will be kept through cell phone electronic messages to remind and reinforce participant attendance at follow-up encounters. Thus, attrition will be recorded in order to verify whether there are differences among students that remained in the program.

One of the strengths of the present study is conducting the intervention by means of a hands-on cooking class series, as opposed to providing a series of cooking demonstration classes. While there is a high staff ratio to assist the participants, the study team assumed that this approach is important for the development of hands-on cooking skills. As a strategy for future program implementation the team would consider a train the trainer model with supervision for interested students. By expanding the trainer pool at a university or like setting the replicability of hands-on cooking classes may be manageable. Studies have suggested that changes in behaviors, attitudes and knowledge about cooking are more substantial among those who have had hands-on cooking classes when compared to those who only participated in expository lectures or classes with a specific interface, as a television [29–31, 72].

NCK class encounters take place in a real home kitchen type setting. Thus, these characteristics may allow for the application of the program in other university types of environments. The instrument employed in the original CWC program was validated for the population of the study that, in turn, was culturally adapted and validated for Brazil [67]. Taking into consideration that few culinary intervention studies use validated and/or adapted instruments with the target population [23], the design of the present study follows methodological rigor.

Furthermore, this study made use of an instrument that was developed specifically for the intervention program. This instrumentation included components to evaluate healthy eating and the cooking practices that were practiced during the hands-on cooking classes, such as, the blanching technique.

It is well known that sustained impact studies of culinary intervention with adults are scarce in the literature [29, 34, 35]. The results of this study, which uses a randomized, control design and with a six month follow-up culinary intervention model will allow high quality evidence to evaluate the impact of the NCK program, based on the CWC program, on participants’ eating habits and cooking behavior. This is the beginning of a program that aims at reaching the entire university community. It is the first cooking skills intervention study devoted to the university community in Brazil. The program may also contribute to the scarce evidence in the literature about the effectiveness of culinary intervention studies with a follow-up period in adults.

## Abbreviations

AAFV: Accessibility and Availability of Fruits and Vegetables Index
BMI: body mass index
CA: Cooking Attitude
CBAH: Cooking Behavior away from home
CBH: Cooking Behavior at home
CCT: Knowledge of Cooking Terms and Techniques
CG: Control group
CWC: Cooking with a Chef
IG: Intervention group
NCK: Nutrition and Culinary in the Kitchen
SCT: Social Cognitive Theory
SECT: Self-Efficacy for Using Basic Cooking Techniques
SEPC: Produce Consumption Self-Efficacy
SEVS: Self-Efficacy for Using Fruits, Vegetables, and Seasonings (while cooking)
